## Abstract

**Background:**

Work-related stress shows steadily increasing prevalence rates and has tangible consequences for individual workers, their organizations, and society as a whole. One mechanism that may help offset the negative outcomes of work-related stress on employees’ well-being is recovery. Recovery refers to the experience of unwinding from one's job when not at work. However, employees who experience high levels of work-related stress and are thus particularly in need of recovery tend to struggle to switch-off. Due to the detrimental effects of this prolonged and sustained mental representation of job stressors, interventions promoting recovery may contribute to improvements in employees' mental health.

**Methods:**

In this randomized, waitlist controlled trial, we will investigate the effectiveness of two 6-week online training programs (cognitive behavioral and mindfulness-based). The sample will include employees working at least part-time during regular work hours. Besides the pre-post-follow-up assessments, the trial will include measurement bursts with the goal of examining the underlying mechanisms. We expect that both interventions will reduce work-related perseverative thinking (PT) compared with the waitlist control groups (primary outcome). Also, we expect that both interventions will result in similar improvements, but the underlying mechanisms will differ (process outcomes). In the cognitive-behavioral intervention group, we expect that the main mechanism responsible for lower PT levels will be an increase in recovery experiences across time. In the mindfulness-based group, we expect that the main mechanism responsible for lower PT levels will be an increase in facets of mindfulness across time.

**Discussion:**

In the present study, we will investigate mechanisms underlying assumed changes in work-related PT in great detail. Besides evaluating the overall effectiveness of the two interventions in terms of pre-post-follow-up changes, we will look at the underlying processes at different levels—that is, within days, within weeks, across weeks, and between individuals. Accordingly, our study will offer a fine-grained approach to investigating potential determinants, mediators, and moderators of the processes that may, in the end, be responsible for work-related strain. From a public health perspective, if effective, the online training programs may offer valuable, low-threshold, and low-intensity interventions for a broad range of occupations.

*Trial registration* German Clinical Trials Registration: DRKS00024933. Registered prospectively 7 April 2021. https://www.drks.de/drks_web/navigate.do?navigationId=trial.HTML&TRIAL_ID=DRKS00024933

## Background

### Recovery from work-related stress

Work-related stress refers to a relationship between the employee and their work environment that is appraised as taxing or exceeding their resources and thus endangering their well-being [1]. Work intensity index measuring exposure to work demands shows a stable and high prevalence of demands such as quantitative demands, work pace, and emotional demands over the last few years [2]. The European Commission estimated that work-related stress affects 55.6 million employees in the European Union [3]. Twenty-five percent of them feel stressed for all or most of the time they spend at work [2]. In 2018, a calculation of the overall costs of work-related stress at a national and pan-European level revealed a (substantial) range from US$221.13 million to $187 billion [4]. These numbers are not without consequences. Work-related stress is associated with a number of consequences for employees' physical and psychological health. Such consequences include increased risk of coronary heart disease [5], metabolic syndrome [6], and mental health issues such as depression [7].

Given these numbers and healthcare-related costs, research has aimed to identify protective individual and organizational factors that may buffer the impact of work-related stress. One of the individual protective factors is an employee’s ability to recover from work. Recovery refers to the experience of unwinding from one's job during the time that is not spent at work [8]. The concept captures various mechanisms that counterbalance employees' reactions to job demands and help them maintain work-related well-being and health [9]. The psychophysiological systems are activated during work in response to job demands. Such reactions to job demands are functional in the first place. They are adaptive for the completion of work chores. But during the time that is spent not working, these reactions should return to a baseline level, that is, a level that appears in a situation in which no particular work demands are made on the individual [10]. Hence, whereas short-lived reactions are adaptive, prolonged and recurring experiences might be potentially harmful. Recovery has been identified as a mediating process between an individual’s responses to stressful work-related experiences and mid- and long-term mental health. Here, recovery is the mechanism that prevents allostatic load [11]. In this vein, recovery has demonstrated advantageous effects for reducing the negative consequences of work-related stress [for a meta-analytical review, see, e.g., 12]—and, conversely, it has shown positive relations with measures of well-being [e.g., 13–15].

Importantly, research has differentiated two complementary conceptualizations of recovery: recovery as a process and recovery as an outcome [8, 15, 16]. Studies investigating recovery as a *process* have mostly focused on the question of whether different experiences and strategies are more or less successful at improving well-being. The earliest approaches to recovery focused on examining the roles of various activities employees engage in when they are not at work. In such approaches, non-work activities are grouped into (a) "low-duty activities" that may promote recovery (e.g., socializing, physical activity) and (b) "high-duty activities" that may further impair recovery (e.g., child care) [15, 17]. Later studies have tended to focus on the experiences that underlie non-work activities, such as detachment, relaxation, mastery, and control. The roles that these experiences play in determining employee well-being have been investigated in general, and during specific time frames, such as breaks during the day [20], evenings [18], weekends [19] and holidays [21]. Moreover, several meta-analyses and reviews have shown that recovery experiences are positively related to, for example, mental health and well-being and are negatively related to measures of fatigue, exhaustion, or negative affect [12, 15, 22].

Among these recovery process variables, psychological detachment has been identified as a central recovery experience [9]. Etzion et al. [23] defined detachment as “the individual’s sense of being away from the work situation” (p. 579). Hence, detachment goes beyond purely "being physically away" from work. It implies a context-specific experience of not thinking about work-related issues and not being involved in work-related tasks [9]. Whereas this definition of psychological detachment refers primarily to the absence of something, Sonnentag and Fritz [9] emphasized that it includes "the experience of being mentally involved in any other content area" (p. S74) or even thinking of nothing in particular as is a common goal in meditative approaches. Although detachment is often examined along with the other three recovery experiences (i.e., relaxation, mastery, and control), it reflects the most central aspect in models such as the Stressor-Detachment-Model [9] and the DRAMMA-Model [where DRAMMA stands for detachment-recovery, autonomy, mastery, meaning, and affiliation; 24]. Despite their substantial bivariate correlations, the experiences represent distinguishable aspects of the recovery process and should not be used interchangeably [15]. In this study, we will focus mainly on the role of psychological detachment but will examine the other three experiences as potential process variables that may contribute to detachment.

Besides recovery processes, a different approach of looking at recovery refers to the *outcome* or the result of switching-off during non-work time. The outcome of recovery can be conceptualized in terms of psychological, physiological, or behavioral measures. For example, psychological aspects of recovery have been assessed in self-reports with constructs such as the "state of feeling recovered" [25]. Here, feelings of replenishment (e.g., feeling "recovered mentally" or "well-rested") serve as indicators of (successful) recovery processes [25] or are examined as a direct result of engaging in recovery activities [26]. Interestingly, such an outcome of recovery processes conceptualized as a "state of being recovered" demonstrated only small to moderate associations with the preceding process of detaching from work in a recent meta-analysis [15]. Moreover, detachment and the state of feeling recovered have shown differential meta-analytical effects on various measures of well-being and performance (e.g., positive affect and job performance). Based on these findings, we will include both detachment and the state of being recovered as recovery indicators in our study.

### Work-related perseverative thinking

Perseverative cognition or thinking (PT)—also referred to as repetitive negative thinking—is an umbrella term for the cognitive processes that underlie various emotional disorders. It has been defined as "the repeated or chronic activation of the cognitive representation of one or more psychological stressors" [27] (p. 114). Hence, PT is characterized by uncontrolled (i.e., at least somewhat intrusive), repetitive, and difficult-to-disengage-from thinking about concerns, problems, and experiences [28]. PT encompasses rumination (i.e., thoughts that focus primarily on the past) and worry (i.e., thoughts that are related primarily to the future). Accordingly, PT occurs before or after stressful events [27], and it extends the adverse effects of these events to times when the stressor is no longer or not yet present. These prolonged experiences of stressors are relevant for individual well-being and strain (reactions) because the sustained cognitive representations may produce physiological responses that are similar to those that occur during the stressful events themselves [29].

Work events represent one type of stressful event that is potentially relevant for PT. In recovery research, studies have investigated repetitive thinking concerning work-related issues in terms of work-related rumination [30]. Similar to the findings for "general" PT in the domain of occupational health, research has found that work-related rumination mediates (the appraisal of) stressful events at work and depressive symptoms [31] and sleep complaints [32]. Hence, in the context of recovery research, PT focusing on work-related issues should be considered a risk factor.

In this vein, work-related PT may reflect an experience that is strongly associated with—or is a form of—unsuccessful recovery (and in particular detachment). Someone who is engaging in PT about work cannot at the same time be detached from work, and someone who is detached from work cannot at the same time engage in PT about work. Despite the high degree of conceptual overlap between work-related PT and psychological detachment, correlations between the two constructs have been moderate [30, 33]. Also, at least cross-sectionally, work-related PC (measured as affective rumination) and detachment are empirically distinguishable [30].

Several scenarios may explain the empirical uniqueness of work-related PT and detachment. First, individuals may find that they are not detached but are still not experiencing repetitive and intrusive thoughts about work. This situation occurs, for example, when individuals work in the evenings or reflect positively on work-related events during their non-work time. Second, individuals may repetitively think about future events or situations at work. This type of PT refers to worrying (often combined with feelings of anxiety) but not rumination about past or more or less current events. However, future-oriented worrying is not well-represented in questionnaires that are designed to measure (affective, past-oriented) rumination. Stated differently, individuals may indeed have trouble winding down and may worry about future events, but this association will remain undetected when PT is measured in terms of rumination (that focuses on past events). Third, some instruments that assess work-related rumination by including adjectives that are indicative of activated negative affect such as nervous or angry [34] presume that employees experience activated negative states [35]. In our view, negative activation and PT should not be merged into single items. Negative activation and PT are co-occurring albeit potentially distinct experiences. Even for constructs that may co-occur in general, merging them into single items leads to measurement issues when used as a state assessment. In a given moment, individuals may experience either or only one of the relevant phenomena, thus raising questions about the response's validity, that is, whether the responses pertain to the activated negative affect, to PT, or to both.

To sum up, both psychological detachment and work-related PT capture non-work experiences that are linked to mental health and psychological well-being [15]. Considering how essential switching-off after work is and how detrimental the effects of PT are for the vast majority of the working population, it seems relevant to look for ways to facilitate detachment and reduce PT in employees. Hence, there is a need to better understand the underlying processes that impair recovery and serve to maintain work-related PT. In this way, we will be able to design new intervention approaches and refine the existing ones.

### Interventions promoting recovery and reducing work-related perseverative thinking

In 2011, Cropley and Zijlstra raised the concern that "there is a distinct lack of studies that have put forward interventions to help people to switch-off, unwind and recover post work" [36] (p. 495). Similarly, Ebert and colleagues (2015) stated that given that interventions for individuals with work-related mental health problems are more effective when work-related aspects are considered, "the limited amount of intervention research on combined interventions that target recovery by improving effective psychological detachment from work and sleep is surprising" [37] (p. 1241).

Meanwhile, various approaches have been designed and evaluated. Several interventions have successfully addressed detachment or repetitive work-related thinking directly [37, 38]. Others have focused on other constructs, such as improving boundary management [39], stress management skills [40], or mindfulness [41]. Hence, in this second group of interventions, increasing detachment or reducing PT was not the primary goal, but these interventions fostered detachment nevertheless.

A recent meta-analysis of interventions that were aimed at fostering detachment [42] stated that, on average, the existing heterogeneous intervention approaches yielded a positive small to moderate effect (*d* = 0.36) on detachment. Interventions that included multiple strategies, such as engagement in recovery activities, boundary management, mindfulness, and more general emotion regulation techniques, were the most successful. In addition, interventions lasting more than 2 weeks and with a higher dosage (in total more than 4 h) were more successful than briefer and lower dosage trainings.

### Combining web-based interventions with experience sampling methodology

In intervention research, there has been an increase in various web-based delivery formats in recent years. Web-based formats include, for example, online interventions with or without additional app support or interventions with varying levels of guidance. Such web-based approaches are generally associated with improvements in participants’ health. Phillips et al. [43] systematically reviewed 50 randomized controlled trials involving web-based formats and found treatment effects with Hedges’ *g* values ranging from 0.30 (for depression) to 0.70 (for insomnia). In recovery research, formats other than face-to-face formats (including web-based formats) yielded an average effect size of *d* = 0.45 [42].

Web-based interventions have numerous advantages. They are highly compatible with participants' daily life obligations due to the self-determined timing, duration, and location of interventions. Also, they are self-administered and are thereby mostly anonymous. These characteristics reduce the burden for individuals who have tight and varying schedules, are fearful of social evaluations, or might avoid or might not profit equally from face-to-face interventions due to social fears and specific therapy alliance problems [44].

From an evaluation perspective, web-based designs make it easier to match the frequency of the intervention with the frequency of the experience of interest [45]. In contrast to face-to-face interventions, participants in web-based interventions have access to the contents of the intervention in their daily lives and can coordinate the activities with their own daily routines. This allows participants to engage with the contents of the intervention whenever they need it most. For example, when addressing recovery, participants might look for supportive contents in the evenings after work. In web-based interventions, this is made feasible by monitoring the progress of the intervention with active and passive experience sampling measures, that is, daily or weekly self-report assessments of the fluctuating constructs combined with sensor-based data. The advantages of web-based interventions may be further enhanced in designs in which several more intensive phases of data collection (i.e., measurement bursts; [46]) are combined into one longitudinal study.

### Investigating processes

Complex intervention designs allow researchers to examine the underlying change mechanisms in more detail [47]. Given that unwinding is an experience that fluctuates strongly within individuals across days, we need intervention designs that capture these fluctuations and match the intervention's evaluation more closely with the behavior of interest [45]. With a pre-post-follow-up design, both the fluctuations and the trajectory of change remain unknown. By contrast, more frequent assessments paralleling the course of the intervention may reveal when the changes occur. For example, a recent mindfulness intervention study [48] found that changes in detachment followed a log-linear trajectory. This finding is in line with the dose–effect model in psychotherapy [49]. In essence, this model predicts the greatest improvements in the first phase of an intervention, followed by a phase of more stable (but improved) levels of detachment. Designs with additional assessments shed light on such trajectories of change and advance our understanding of both nonlinear improvements and phases that can be useful for stabilizing and reinforcing the change that is achieved.

With designs that include various measurements along the way, researchers can simultaneously analyze within-person processes and individual differences in these processes. For example, at the within-person level, negative activation (i.e., unpleasant mood and unpleasant discrete emotions, e.g., anger, sadness, or anxiety) and high tense arousal may represent the key variables that impair recovery [50] and serve to maintain PT. Negative activation (NA) may impede recovery because individuals experience and relive job stressors even after long periods of not working and might not even recover fully during sleep due to its job-related fragmentation [51]. Also, NA and both recovery and PT may be reciprocally related (i.e., not only does NA impede recovery/maintain PT, but low recovery/high levels of PT may, in turn, maintain NA). Shipp and Cole [52] argued that "considering the role of feedback loops, cycles, and spirals is a natural next step for within-person explanatory research" (p. 12). The reciprocal relations between recovery and PT on the one side and NA on the other side may create a loss cycle [53]. This sustained mental and affective arousal may, in turn, be associated with symptoms of strain, such as impaired sleep [54].

Intervention studies including intensive longitudinal assessments and measurement bursts create entirely new avenues for investigating within-person processes. Designs with multiple well-timed assessments or measurement burst designs are basic preconditions for looking at processes and mechanisms as they unfold in daily life. But it is the combination of such designs with interventions that puts the assumed processes to the test. Similar to an implementation of two experimental groups in a pre-post-follow-up design, a direct comparison of two different treatments allows for the strengthening of conclusions about the underlying mechanism and the boundary conditions that restrict or boost training effectiveness. Hence, in this trial, we will build upon previous research on recovery interventions [42] by implementing two intervention groups: one with a cognitive-behavioral focus and one with a mindfulness-based approach (for more details about the contents of the intervention, see below). So far, a similar direct comparison was planned in one study [55] but without the specific focus on within-person processes and trajectories of change.

In sum, by taking dynamic within-person processes into account, with our study, we aim to shed more light on the development, trajectory, and maintenance of recovery in daily life. Further, our complex design will allow us to examine and compare the effects of the two interventions on these processes. On the basis of previous literature [42], in both intervention groups, we expect improvements in recovery processes, negative activation, and strain measures at the daily level. Here, changes refer to both the respective levels of the constructs and their respective associations. The mechanisms responsible for these improvements may differ across the experimental groups. In the CBT-based group, we expect the mechanism responsible for reducing work-related PT to be an increase in recovery experiences because the contents of the intervention pertain to these strategies (e.g., boundary tactics and recreational activities). In the mindfulness-based group, we expect the main mechanism responsible for lower levels of work-related PT to be increases across time in affect regulation strategies (e.g., reappraisal) and the facets of mindfulness such as non-reactivity and acting with awareness.

## Research goals

The first goal of this randomized controlled trial is to compare the efficacy of two online training programs promoting recovery from work. We hypothesize that participants in the two experimental conditions (CBT-based and mindfulness-based training) will experience lower levels of work-related PT (primary outcome) after the intervention. No prediction can be made from previous literature as to which of the two interventions would be more effective. Therefore, we assume that the two experimental conditions will not differ with regard to their effectiveness in reducing the primary outcome.

The second goal of the present study is to explore the mechanisms related to recovery from work and its improvement on a daily level. Hence, using the data from the experience sampling phases of the study, we will investigate within- and between-day variables and processes that may account for the overall effect of the intervention—and, in addition, may further qualify the expected effect.

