#### Outcome assessments

We will evaluate the effectiveness of both interventions by comparing the respective levels of the outcome variables at pretest, posttest, and a 3-month follow-up. The pretest will take place before the first week of experience sampling and the intervention. The posttest will take place in the week after the intervention. The follow-up will take place 3 months after the posttest to evaluate whether changes in work-related PT remained stable over this more extended period or reverted to their pre-intervention levels. We will ask the participants to evaluate all primary and secondary outcomes using a time frame of 2 weeks.

The primary outcome in these pretest, posttest, and follow-up assessments is *work-related PT*. We will measure work-related PT using a combination of three worry items [60], four rumination items [28], and two brooding/rehearsal items [61]. Items have been adapted to the work context. The response scale ranges from 1 (not true at all) to 5 (very true). For a complete list of items, see the supplementary online materials on the OSF: https://osf.io/jzt6g/. This group of items has not been used in this combination as an indicator of PT before. We therefore evaluated the measure in terms of model fit and convergent and discriminant validity in a sample of 202 employees working at least part-time. A unidimensional model fit the data well (CFI = 0.98; TLI = 0.97; RMSEA = 0.07; SRMR = 0.03), and the pattern of correlations with (a) measures of similar constructs, such as affective rumination [35], detachment [62], and (b) relevant correlates (e.g., emotional demands, fatigue, stress, and affect) was meaningful and as expected. The internal consistency of the scale was good: McDonald’s ω = 92.

Secondary outcomes will be the following work and mental health variables, which are conceptually and typically empirically associated with work-related PT.

*Detachment*. We will measure psychological detachment with a four-item subscale from the Recovery Experience Questionnaire [62]. The rating scale ranges from 1 (not true at all) to 7 (very true).

*State of being recovered.* State of being recovered will be measured with four items proposed by Sonnentag and Kruel [63]. On the pretest, posttest, and follow-up questionnaires, we will ask the participants how rested and refreshed they felt during the last 2 weeks using a 5-point scale ranging from 1 (not true at all) to 5 (very true).

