### Data analyses

Our research goals refer to different levels of the data. Besides evaluations of the interventions’ efficacy, one part of our research involves hypotheses on the within-day level. By contrast, others focus on the same processes between days and several weeks. We will address the complexity of our data by applying various statistical approaches.

To evaluate changes across time in primary and secondary outcomes, we will use the pretest, posttest, and follow-up measures. These measures represent indicators of latent variables estimated separately in the two experimental groups and the two waitlist control groups combined. Using the latent variables (latent states), we will set up Multigroup Latent Change Models (with baseline-change and neighbor-change variants). Latent Change Scores from (a) pretest to posttest and from pretest to follow-up (baseline-change) and (b) from pretest to posttest and from posttest to follow-up (neighbor-change) will provide information about the effect sizes from pre to post and on the maintenance of the effects from posttest to follow-up [86]. To estimate the models, we will use the Bayes estimator as implemented in Mplus [87]. We will determine the convergence diagnostic [88], evaluate potential convergence issues by doubling the number of iterations, and visually inspect histograms for all parameters and the trace plots for the Markov chains. For the difference between the pre-post change scores in both experimental groups, we will set up an informative prior with a normal distribution, a mean of zero, and a small variance, that is, *N*(0, 0.010). This prior corresponds to the assumption that the change scores in the two groups should be equal, implying similar efficacy between the two interventions. A small variance around the mean of the prior will reflect our confidence that the difference between the change scores will be minimal but will allow for small differences [89]. This distribution implies that 95% of the standardized differences in the means ranges from -0.2 and 0.2. Accordingly, the efficacy of the two interventions will be considered equal if the standardized difference in the latent change scores based on the posterior distribution lies within a range of -0.2 and 0.2.

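### The equality prior and the ±0.2 rule are not limited to the primary outcome, although equal effectiveness is assumed only for that outcome

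*Protocol article*

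**What the plan says.** The Research goals section says that earlier work gives no basis for predicting which programme is better, and concludes: "Therefore, we assume that the two experimental conditions will not differ with regard to their effectiveness in reducing the primary outcome". The primary outcome is work-related PT.

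The Data analyses section opens its efficacy paragraph with both classes of outcome: "To evaluate changes across time in primary and secondary outcomes, we will use the pretest, posttest, and follow-up measures". It then describes multigroup latent change models estimated with the Bayes estimator. Still in that paragraph it continues: "For the difference between the pre-post change scores in both experimental groups, we will set up an informative prior". The prior is normal with mean zero and variance 0.010, and the section explains its width: "This distribution implies that 95% of the standardized differences in the means ranges from -0.2 and 0.2". The two programmes are to be considered equal if the standardised difference in latent change, based on the posterior, lies between -0.2 and 0.2. Neither the prior nor the rule names an outcome.

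The Outcome assessments section lists seven secondary outcomes: detachment, state of being recovered, fatigue, sleep quality, affective well-being, negative activation and stress. Of detachment it says: "We will measure psychological detachment with a four-item subscale from the Recovery Experience Questionnaire".

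**The concern.** The prior encodes an assumption that the article states for one outcome, while the paragraph containing it sets out the analysis of eight. For the seven secondary outcomes the article gives no reason to expect equal change in the two programmes. A prior of this width is not neutral: its SD is 0.10 on the standardised scale, about the same as the sampling error of a programme difference at the planned sample size.

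If the paragraph is followed as written, every secondary comparison between the cognitive-behavioural and the mindfulness programme is pulled towards zero by an assumption made for PT alone. A real difference in, say, sleep quality would be understated, would be detected less often, and might be labelled equal.

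**Working it through.** **Inputs from the article**
- Total sample 600, with up to 20% lost before posttest, leaving 480 (Participants and recruitment).
- Two thirds of participants go to the two experimental arms: 600 × 2/3 ÷ 2 = 200 per programme, and 200 × 0.8 = 160 at posttest.
- Prior variance τ² = 0.010; equality range ±0.2 (Data analyses).

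**Assumptions.** Normal approximation to the posterior. The pre-post correlation r is not given, so a range is shown.

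**The article's own figure.** 1.96 × √0.010 = 0.196, which agrees with the stated 95% range of -0.2 to 0.2. So 0.010 is a variance, as the article says.

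**Shrinkage, SD of change = 1**
- Sampling variance of the difference: s² = 2/160 = 0.0125, SE = 0.112.
- Weight on the data: τ²/(τ² + s²) = 0.010/0.0225 = 0.444.
- Share removed: 1 − 0.444 = 0.556, or 56%.
- Posterior SD: √(1/(1/0.010 + 1/0.0125)) = √(1/180) = 0.0745.

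The share removed depends on the number per programme: 62.5% at 120 (equal four-arm allocation, which another sentence in the same section suggests), 59.5% at 136, and 50.0% at 200 (no dropout).

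**A true difference of 0.30 on this scale**
- Average posterior mean: 0.444 × 0.30 = 0.13.
- The 95% interval excludes zero when the observed difference exceeds 1.96 × 0.0745/0.444 = 0.329 in size. For X ~ N(0.30, SE 0.112) the probability is 0.40. With a diffuse prior the threshold is 1.96 × 0.112 = 0.219 and the probability is 0.77.
- The 95% interval covers the true value in 34% of trials.
- Equality judged by the posterior mean: the observed difference must lie within ±0.2/0.444 = ±0.45, probability 0.91. With a diffuse prior the limit is ±0.2, probability 0.19.
- Equality judged by the whole 95% interval: the posterior mean must lie within ±(0.2 − 1.96 × 0.0745) = ±0.054, so the observed difference within ±0.121, probability 0.055 (about 6%). With a diffuse prior the half-width of 0.219 already exceeds 0.2, so this label could not occur.

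**Standardising on the baseline SD instead.** Then Var(change) = 2(1 − r) and s² = 2 × Var(change)/160. For a true difference of 0.30 in these units:

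| r (assumed) | s² | share removed | average posterior mean | interval excludes zero: prior / diffuse |
|---|---|---|---|---|
| 0.2 | 0.0200 | 67% | 0.10 | 10% / 56% |
| 0.4 | 0.0150 | 60% | 0.12 | 26% / 69% |
| 0.5 | 0.0125 | 56% | 0.13 | 40% / 77% |
| 0.6 | 0.0100 | 50% | 0.15 | 59% / 85% |
| 0.7 | 0.0075 | 43% | 0.17 | 81% / 93% |
| 0.8 | 0.0050 | 33% | 0.20 | 97% / 99% |

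**The case against.** The best reply is that the prior was meant for PT only. The article's one express no-difference assumption names the primary outcome, the prior is justified by that kind of assumption, and Participants and recruitment links the latent change model to the primary outcome. This may well be the intention, and it stands to this extent: that the prior applies to detachment or any other secondary outcome is inferred from the missing restriction and is stated nowhere. But the Data analyses paragraph applies the same model to both classes of outcome and fixes the prior, its variance and the decision rule without exception. An analyst following it would apply them throughout.

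A reader might also infer that the prior undermines the trial's hypothesis of similar efficacy through different mechanisms, since the article says "The mechanisms responsible for these improvements may differ across the experimental groups". The article does not support that. Research goals and Data analyses place the mechanism questions mainly in the experience-sampling data and dynamic structural equation models, for which no such prior is stated. The article expects recovery processes to improve in both programmes and predicts no difference between them in mean detachment; different mediating paths do not require one. Among the mechanism variables, only detachment is a listed secondary outcome. Table 1 groups secondary and process measures under one heading, which does not show that mindfulness facets or affect regulation receive the prior.

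Two objections to the size also have weight. First, a flat statement that more than half of a difference is removed would be too strong, because the share depends on the standardiser, r and retention. Second, a difference of 0.30 between two active programmes is large beside the average intervention effect on detachment of d = 0.36 that the article cites. The proportion removed, however, is the same whatever the true difference.

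**Conclusion.** The point holds as a mismatch of scope. Equal effectiveness is assumed for work-related PT alone, whereas the prior and the ±0.2 rule stand unrestricted in the analysis of primary and secondary outcomes. Applied as written at about 160 per programme, the prior removes roughly one third to two thirds of a secondary programme difference in pre-post change.

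The loss of power is marked at low to moderate pre-post correlations and small at r = 0.8, where the understatement of the difference is still one third. How often a true 0.30 would be called equal cannot be settled from the article: about 91% if the rule uses the posterior mean, about 6% if it uses the whole 95% interval (both on the SD-of-change scale). The 91% should therefore not be quoted alone.

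These figures rest on a normal approximation, 20% loss, two-thirds allocation to the programmes and a prior acting on the standardised scale. They concern the pre-post comparison between programmes on secondary outcomes. Whether the prior is suitable for PT itself is a separate question. The correction is worth making, but it does not threaten the primary comparison with the waitlist groups.

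**What to change.** In Data analyses, state that the N(0, 0.010) prior and the ±0.2 equality rule apply to work-related PT only, in line with Research goals. For the listed secondary outcomes, and for any process outcome analysed with the same latent change model, use a diffuse prior on the programme difference. Report that difference with its 95% credible interval and without an 'equal' label.

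This takes a sentence in the plan and the removal of the prior from the secondary-outcome code; no further data are needed. The cost is precision: at 160 per programme and SD of change = 1, the interval half-width rises from 1.96 × 0.0745 = 0.146 to 1.96 × 0.112 = 0.219. That narrower interval comes from an equality assumption the article does not make for these outcomes.
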